### Public health engagement in licensing

Following the enhancement of their statutory roles, many professionals with an interest in reducing alcohol-related harms have increased their engagement with premises licensing [44–50]. As well as public health teams in local government in England, in Scotland this work has involved NHS public health departments, NHS professionals with a strategic remit to reduce alcohol-related harms, and professionals based in ‘Alcohol and Drug Partnerships’. Hereafter, for ease of writing, we use the term ‘Public Health Team’ or ‘PHT’ to describe any combination of these groups.

Research in Scotland found that early public health involvement achieved mixed results, with some areas introducing large-scale overprovision policies, and others strongly resisting public health engagement [44, 45, 51]. In England and Wales, PHTs have also faced challenges in adapting to the licensing environment [32, 41, 50, 52]. PH engagement in licensing forms part of a wider, interactional system involving ‘responsible authorities’ (such as fire, police and child protection authorities as well as health bodies), licensing committees, the alcohol trade and, in some cases, the general public. In engaging with this system, and with support from national organisations such as Public Health England (PHE) and Alcohol Focus Scotland (AFS), PHTs have developed a range of approaches [39, 53].

PHTs may, for instance, make representations directly to licensing authorities, provide data in support of a representation by the local police or Trading Standards, respond to consultations on cumulative impact policy or, as has been more common in Scotland, take the lead in developing the case for the establishment of overprovision areas [44, 49, 51]. Some PHTs have developed processes for reviewing and responding to licence applications, collated local datasets on outlet density and alcohol-related harms, supported the development of licensing policies, involved local communities, or directly engaged with licence-holders [46, 47, 49, 51, 54, 55]. These approaches are used to varying degrees of intensity and in varying combinations in local areas across England and Scotland, creating a natural experiment that has yet to be robustly evaluated and which is the focus of the current study.

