### ExILEnS study aim, research questions & objectives

This study will, for the first time, seek to robustly measure PHTs’ involvement in the alcohol premises licensing system over time, and assess whether greater levels of involvement are associated with reduced alcohol-related harms. Given the complexities referred to above, the study will include a strong focus on processes and mechanisms, as well as assessing health, crime and cost-related impacts.

The aim of this study “Exploring the Impact of alcohol premises Licensing in England and Scotland” (ExILEnS) is:To critically assess the impact and mechanisms of impact of public health stakeholders’ engagement in alcohol premises licensing on alcohol-related harms in England and Scotland from 2012 to 2018 by comparing areas with differing types and intensities of engagement.

The primary research question is:Does intensive public health engagement in alcohol licensing reduce alcohol-related harms, in local authorities where such activity exists, compared with authorities with low levels of, or no, such activity?

Secondary research questions are:2)What are the costs and cost-savings, mechanisms of action, and impact on health inequalities of public health engagement in licensing?3)How do engagement, processes, acceptability, and outcomes vary between Scotland (where a public health objective for licensing exists) and England and from PHTs and licensing perspectives?

This study will contribute to understanding the potential mechanisms of effect of such PHT activity within a complex system and is intended to generate detailed, policy-relevant evidence that can be acted on locally, as well as informing potential national legislative changes and, where appropriate, international licensing regimes.

The study has four sets of objectives addressed by four corresponding work packages. The objectives are illustrated in Table 1.

**Table 1 Tab1:** Work Packages & Objectives

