### Recruitment and allocation

#### Intervention areas

The ‘intervention’ in our study is defined as the presence of a PHT that has been active across multiple aspects of public health engagement in alcohol premises licensing. The unit of analysis for each selected area will be a lower-tier local authority area in England or a single licensing board area in Scotland.

We will recruit 20 PHTs who have been actively seeking to influence alcohol licensing in at least one local authority/licensing board area under their remit. Where a PHT is active in several local areas, the one in which they deem themselves to be most active will form the ‘intervention’ area for the study. The study will also identify 20 ‘control’ local authority areas where little or no PHT involvement in licensing has occurred. Six intervention and matched control areas in Scotland will be included along with 14 intervention and matched control areas in England, giving 40 areas in total.

All PHTs were informed about the proposed study by PHE and AFS prior to funding being secured and were invited to express interest in being involved (44 areas expressed interest at that stage). We will issue further calls for expressions of interest by email, promote the study through events organised by PHE and AFS and via relevant other organisations and events such as the Institute of Alcohol Studies, the National Licensing and Public Health Network, and invite participation through direct contacts with local areas where members of the team and colleagues have previously worked. We will build on all of these networks to publicise the opportunity to participate in the study.

From those areas that have expressed interest, we will select active intervention areas based on a combination of the following:advice from expert bodies including our study advisory group;published reports and case studies [44, 47, 61–63]publically available information on involvement in other licensing initiatives (such as the home office initiative ‘local alcohol action areas’ [64, 65]);prior research by members of the team and colleagues e.g. [49, 51, 66]scoping calls with local areas to clarify levels of activity since 2012 and continued interest in participating in the research.

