### Power calculations

No quantitative data is available on the effect of public health engagement in licensing on alcohol-related harms. The assumed mechanism by which such engagement might reduce harms however, is by influencing the local licensing system. Statistical power estimations therefore have been based on effect sizes from two recent studies of the effect of alcohol premises licensing on alcohol-related hospital admissions and reported crime rates at the level of ‘lower tier local authority’ (LTLA) in England [28, 29]. Areas with active alcohol licensing policies had an average additional 2% (95% CI -3%:-2%) annual reduction in alcohol-related hospital admissions in the period up to and including 2013 compared to those without such policies [28]. Similarly, for the period up to 2013, an additional 4–6% annual decrease was seen in alcohol-related violent crimes, sexual crimes and public order offences in areas with active licensing policies compared to those with none [29].

We used the methodology developed by Edland for power calculations of linear mixed effects models with random slope [68]. Based on the previous studies, we conducted separate sample size calculations for alcohol-related hospital admissions and reported crime rates. For both analyses we assumed a standard level of statistical significance α (5%) and statistical power β (80%), and further assumed a 9-year follow-up (2009–2018) and a two-sided alternative. Table 4 outlines the detectable effect size with 20 intervention and 20 control areas.

**Table 4 Tab4:** Sample size data

	Expected average effect size %/year (slope)	Between-slope variance	Residual variance model	Number of areas in each group
*From previous study of impact of licensing on alcohol-related crime* [29]				
Crime rates^a^	−4.00% (−0.04)	0.003	0.03	29
	−5.00% (−0.04)	0.003	0.03	19
	−6.00% (−0.06)	0.003	0.03	13
*From previous study of impact of licensing on alcohol-related hospital admissions* [28]				
Rates	−2.31% (−0.229)	0.110	0.011	34
*Current study - minimum detectable effect size with proposed sample size*				
20 areas per group	−3.00% (−0.296)	0.110	0.011	20

^a^Effect size is a range between 4 and 6% as estimated by d Vocht et al. (2016) using quadratic trends

Based on Table 4, we expect the study to be able to detect effects on our outcomes within the range found in previous observational studies with 20 intervention and 20 control areas.

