As public health engagement in this area is potentially resource-intensive, findings from ExILEns will inform decisions on about whether this activity represents the best use of time for public health teams. If it is shown that there are measurable benefits, this will help to make the case for greater investment in public health capacity and/or potentially greater legislative support through the introduction of a public health objective in England. If, however, our findings suggest limited effects of public health activity in this arena, or little potential for licensing policy to materially affect alcohol-related harms, then this will contribute to current debate around more substantial legislative changes [84]. Should this study have null findings, this may, therefore, be as significant in policy terms as a demonstration of positive effects.

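### The power section carries licensing-policy effects undiscounted to a public health engagement contrast, and claims wider detectability than 20 areas per group supports

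*Protocol article*

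**What the plan says.** The Power calculations section states that no quantitative data exist on the effect of public health team engagement. It assumes that engagement acts through the local licensing system and concludes: "Statistical power estimations therefore have been based on effect sizes from two recent studies of the effect of alcohol premises licensing". The borrowed contrasts are active licensing policy against no such policy. The admissions effect is about 2% per year (2.31% in Table 4). The crime effect is 4-6% per year, seen "in areas with active licensing policies compared to those with none".

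The study's own contrast is different. The primary question sets intensive engagement against its absence or near-absence: "compared with authorities with low levels of, or no, such activity". Controls are "areas where little or no PHT involvement in licensing has occurred". Table 2 matches on outlet density, among other covariates, but not on cumulative impact or overprovision policy.

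Table 4 asks for 29, 19 and 13 areas per group for crime effects of 4, 5 and 6% per year, and 34 per group for the 2.31% admissions effect. It gives 3.00% per year as the smallest detectable effect with 20 per group, using the admissions variances. For that sample size, the section closes: "we expect the study to be able to detect effects on our outcomes within the range found in previous observational studies".

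**The concern.** There are two separate problems.

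First, the theory of change places licensing between engagement and harm. On that pathway the engagement effect equals the licensing effect multiplied by how far engagement changes licensing. Table 4 uses the licensing effect whole. A control area may have an active licensing policy for reasons unrelated to its public health team, and an intervention area may not have secured one. The Background gives reason for caution. It reports mixed early results in Scotland, and of England and Wales it says that "PHTs have also faced challenges in adapting to the licensing environment".

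Second, the closing sentence reads as if 20 per group covered the earlier range. Table 4 asks for more than 20 per group for two of its four borrowed effects.

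At stake is how a null result is read. The Discussion treats null findings as potentially as important for policy as positive ones. Among the possible conclusions it names "little potential for licensing policy to materially affect alcohol-related harms". If the engagement contrast has modest power, a null result could be expected even where licensing works and engagement partly drives it.

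**Working it through.** **Inputs.** All are from the Power calculations section and Table 4: two-sided 5%, 80% power, 2009-2018, 20 areas per group.
- Admissions: slope 0.229 (2.31%), between-slope variance 0.110, residual variance 0.011.
- Crime: slopes 0.04, 0.05 and 0.06, between-slope variance 0.003, residual variance 0.03. The 5% row prints its slope as -0.04, but its 19 areas are reproduced only with 0.05, so 0.05 is used.

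**Formula (random-slope model).** n per group = 2(1.960 + 0.842)² × V / slope², where V = between-slope variance + residual variance / Sxx. Sxx is the sum of squared deviations of the time points, in years. Table 4 does not state the number of time points, so two schedules are shown: 10 annual points (Sxx = 82.5) and 40 quarterly points (Sxx = 333.125).

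**Reproducing Table 4.**
- Admissions, annual: V = 0.110 + 0.011/82.5 = 0.11013. n = 15.70 × 0.11013 / 0.229² = 33.0 (stated 34). At slope 0.296, n = 19.7 (stated 20). Quarterly points give almost the same.
- Crime, quarterly: V = 0.003 + 0.03/333.125 = 0.00309. n = 30.3, 19.4 and 13.5 (stated 29, 19 and 13).
- Crime, annual: V = 0.00336. n = 33.0, 21.1 and 14.7, a poorer match for 4% and 5%.

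The plan's figures are reproduced closely enough to work from. Ranges below show both schedules.

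**What 20 per group detects at 80% power.** Slope = 2.802 × √(2V/20).
- Admissions: 2.802 × 0.1049 = 0.294, about 3% per year (Table 4: 0.296).
- Crime: 0.0492 (quarterly) to 0.0514 (annual), about 5% per year.

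**Power at 20 per group for the borrowed effects.** Power = Φ(f × slope / √(2V/20) − 1.96). Here f is the share of the borrowed effect that reaches the engagement contrast. The document gives no value, so f is an assumption shown as a range. Worked case: admissions at f = 1 gives 0.229/0.1049 − 1.96 = 0.22, and Φ(0.22) is about 59%.

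| Borrowed effect per year | f = 1 | f = 0.75 | f = 0.5 | f needed for 80% |
|---|---|---|---|---|
| Admissions 2.31% | 59% | 37% | 19% | 1.28 |
| Crime 4% | 59-62% | 37-40% | 19-21% | 1.23-1.28 |
| Crime 5% | 78-81% | 53-57% | 28-30% | 0.98-1.03 |
| Crime 6% | 91-93% | 69-73% | 37-40% | 0.82-0.86 |

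The last column is the detectable slope divided by the borrowed slope, for example 0.294/0.229 = 1.28. Two of the four effects fall short of 80% before any discount. Only the 6% crime effect leaves room for incomplete transmission.

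**The case against.** The case for the plan is substantial.

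- **The proxy is open.** The section says there are no direct data and explains why licensing effects stand in. A minimum detectable effect holds for any two-group slope contrast with those variances. The closing sentence can be read as claiming only that some effects within the earlier range are detectable: 3% lies at the edge of the quoted interval for admissions, and 5-6% lies inside the crime range. This stands against any charge of a concealed error. It does not supply a transmission assumption, and a reader of that sentence would not learn that the 2.31% and 4% effects fall short.
- **Full transmission is not shown to be implausible.** A reader might infer that it is. The documents give no transmission figure. Selection favours areas with sustained, intensive engagement from early on, which should widen the contrast, and the sentence on mixed Scottish results also reports some large-scale overprovision policies. The supportable word is uncertain.
- **Licensing exists everywhere.** A reader might infer that this alone separates the study from its sources. It does not, because licensing is statutory in all areas and the earlier comparators had it too. The difference is that active licensing policy does not define the groups here.
- **The fraction f is a simplification.** The protocol also lists direct work with licensees and several mechanisms, so f need not be capped at 1. The table does not cover power for the planned six-monthly intensity, pre/post or difference-in-differences analyses. It is illustrative only.
- **The Discussion refers to the whole study's findings.** A reader might infer that it would draw conclusions on licensing policy from a null engagement contrast alone. It does not say so, and a separate licensing intensity score is planned.

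**Conclusion.** The concern holds in a limited form. The planning effects belong to a different exposure, downstream of engagement in the plan's own theory, and are used at full strength with no stated fraction or range. Separately, the closing detectability sentence is broader than Table 4 supports even at full transmission. With 20 per group, the 2.31% admissions effect has about 59% power and needs 33-34 areas per group. The 4% crime effect has about 59-62% power and needs 29 or more.

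The shortfall at f = 1 rests only on Table 4's variances and the normal approximation. It is a sample-size matter, separate from the choice of comparator. The lower figures at f = 0.75 and 0.5 rest on an assumed fraction. At f = 0.5 every borrowed effect has power of 40% or less, so a non-significant result would have a probability of at least 60%.

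It would be wrong to apply f to the 3.00% minimum detectable effect and conclude that admissions need near-complete separation in licensing. That 3.00% is what this design can detect, not what the earlier study found. Measured against the earlier 2.31%, the fraction needed is about 1.28.

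**What to change.** 1. **Power calculations, closing sentence.** Replace it with the detectable effects: at 80% power and 20 areas per group, about 3% per year for admissions and about 5% per year for crime. Say that the earlier 2.31% admissions and 4% crime effects are not detectable at that power. Say also that the borrowed effects are for licensing policy, and that the engagement effect may be smaller if engagement only partly changes licensing.
2. **Table 4.** Add an illustrative sensitivity row from the borrowed effects, with f labelled as an assumption. Power at f = 1 / 0.75 / 0.5 is about 59 / 37 / 19% for admissions 2.31%, 78-81 / 53-57 / 28-30% for crime 5%, and 91-93 / 69-73 / 37-40% for crime 6%. The f needed for 80% power is about 1.28, 0.98-1.03 and 0.82-0.86 respectively.
3. **Before the outcome analysis.** Report the between-group difference in the licensing intensity score, which is already planned for all 40 areas.
4. **Discussion.** State that a null high-versus-low contrast speaks to engagement only. Conclusions on licensing policy should rest on the planned analysis of the licensing intensity score and its confidence interval.

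The cost is wording, one table row and one descriptive comparison of scores already to be collected. No areas or data are added. The downside is a less favourable stated power.

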### Alcohol Availability & Harm

Systematic reviews, and reviews of reviews, have concluded that legislative measures, including control of the ease with which alcohol can be obtained, can be effective in reducing alcohol-related harms [15–17]. These ‘availability’ interventions include limits on the age at which alcohol may be purchased, as well as controls on the number and proximity of outlets selling alcohol (physical availability) and their hours of sale (temporal availability). There is consistent evidence suggesting an association between increased physical and temporal availability of alcohol and higher rates of consumption and associated alcohol-related harms [18–23], including several UK studies [24–27].

Two recent studies found that local authorities in England with a more intensive alcohol premises licensing regime experienced an additional 5% reduction in alcohol related hospital admissions rates from 2009 to 2015 (or 2% annually) [28] as well as an additional 4–6% reduction in public nuisance and alcohol-related crime rates [29], compared with what would have been expected had these local areas had no active licensing policy in place [30]. The density of alcohol outlets has been shown to be higher in deprived areas in both England and Scotland [25, 31]. Whilst the direction of causation for this relationship is unknown, it raises the possibility that alcohol premises licensing policy could have a greater positive impact on health harms in these areas, and even reduce alcohol-related health inequalities [25, 32].

The extent to which increased availability causes alcohol harms, and if so, the mechanisms by which effects are exerted remains unclear, since much of the research is cross-sectional and the validity of measures of the availability of alcohol premises is variable [21, 33–37]. A recent review of 160 studies found that a causal relationship between public health activities, specific local licensing controls, indicators and types of availability and alcohol-related harms is not clear or consistently demonstrated in the literature [33]. The same study noted the difficulty of translating the research into practice, due both to these limitations and the lack of clear theories of change [33]. Examining the relationship between these three sets of variables – public health team activity, the licensing regime, and local level health/crime outcomes – is the core focus of this study.

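### Table 4 carries yearly effects that the power section reports only up to 2013 forward as a constant divergence over 2009–2018; nothing in the protocol supports this, and the stated 80% power depends on it

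*Protocol article*

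**What the plan says.** The Power calculations section bases its inputs on two earlier English studies of licensing policy. For admissions it gives an average additional 2% "annual reduction in alcohol-related hospital admissions in the period up to and including 2013". For crime it states that "for the period up to 2013, an additional 4–6% annual decrease was seen". The Table 4 footnote adds that the crime range was estimated "using quadratic trends".

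The method is one for "power calculations of linear mixed effects models with random slope", and the authors "further assumed a 9-year follow-up (2009–2018) and a two-sided alternative". Each effect enters Table 4 as a single slope per year. The section closes by expecting that 20 areas per group can detect effects in the range of the earlier studies.

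The Background (Alcohol Availability & Harm) describes the same admissions study as showing an "additional 5% reduction in alcohol related hospital admissions rates from 2009 to 2015 (or 2% annually"). It gives the crime effect as 4–6% without calling it annual.

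**The concern.** A single slope difference in a linear random-slope model means that the groups separate by the same amount every year for the whole follow-up. The power section reports its source effects for a period ending in 2013, and it names a crime model in which the yearly difference need not be constant. The protocol does not say why the early yearly rate should persist to 2018, and it shows no case in which it does not.

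If the gap stops widening, the straight line fitted over 2009–2018 has a shallower slope than the one entered, and power falls quickly. This affects how the result is read. The Discussion says that null findings may be as significant for policy as positive ones, and that holds only if power is described realistically.

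**Working it through.** **Inputs.** From the Power calculations section and Table 4: two-sided 5%, 80% power, 20 areas per group. Crime has slopes 0.04, 0.05 and 0.06, between-slope variance 0.003 and residual variance 0.03. Admissions has slopes 0.229 (−2.31%) and 0.296 (−3.00%), between-slope variance 0.110 and residual variance 0.011. Table 3 lists admissions and crime as quarterly, so I used 40 quarterly points, t = 0, 0.25, …, 9.75 years from the start of 2009. The sum of squared time deviations is Sxx = 333.1.

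**Step 1: reproduce Table 4.** With V = between-slope variance + residual variance / Sxx, n per group = 2 × (1.960 + 0.842)² × V / slope².
- Crime: V = 0.003 + 0.03/333.1 = 0.00309, so n = 30.3, 19.4 and 13.5 (printed 29, 19, 13).
- Admissions: V = 0.110 + 0.011/333.1 = 0.11003, so n = 32.9 and 19.7 (printed 34 and 20).

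Table 4 is therefore a constant-slope calculation. The −5% crime row reproduces with slope 0.05, not with the printed 0.04. Ten annual points give 33.0, 21.1 and 14.7 for crime, a poorer match, so the quarterly grid is the better choice.

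**Step 2: slope actually fitted if the gap levels off.** If the gap grows at the entered rate until time c and then stays constant, the fitted slope is the entered slope times k = Σ(t − t̄)·min(t, c) / Sxx.
- Growth to end 2018: k = 1.00
- Growth to end 2015 (c = 7): k = 0.80
- Growth to end 2013 (c = 5): k = 0.52

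**Step 3: power at 20 per group.** SE = √(2V/20), which is 0.0176 for crime and 0.1049 for admissions. Power = Φ(slope × k / SE − 1.96). For example, crime −5% with k = 1 gives Φ(0.05/0.0176 − 1.96) = Φ(0.88) = 81%.

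| Effect per year | Constant to 2018 | Stops end 2015 | Stops end 2013 |
|---|---|---|---|
| Crime −4% | 62% | 44% | 22% |
| Crime −5% | 81% | 62% | 31% |
| Crime −6% | 93% | 78% | 43% |
| Admissions −2.31% | 59% | 42% | 20% |
| Admissions −3.00% | 81% | 62% | 31% |

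If the power section's wording for crime means the start of 2013 (c = 4, k = 0.37), power for crime −5% and −6% is 18% and 24%.

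**Step 4: the Background against the power section.** A reduction of 2% a year for six years compounds to 1 − 0.98⁶ = 11%, not 5%. A total of 5% over six years is 1 − 0.95^(1/6) = 0.85% a year, not 2%. The Background's two admissions figures therefore cannot both describe a constant rate over 2009 to 2015.

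**Step 5: size of the gap assumed.** Over nine years the entered rates compound to about 31%, 37% and 43% for crime (1 − 0.96⁹, 1 − 0.95⁹, 1 − 0.94⁹). For admissions they compound to about 19% (1 − 0.9769⁹) and 24% (1 − 0.97⁹).

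**The case against.** A constant slope difference is the standard input to the method the protocol names, Table 4 labels its input as an average effect, and every power calculation rests on assumptions. The arithmetic is sound: Table 4 reproduces. All of this stands, and the point is about an unsupported assumption, not a calculation error. But an average over a window ending in 2013 is not an average to 2018.

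Several stronger readings are tempting, and the protocol does not support them.
- *Quadratic trends mean the effect was fading.* The footnote gives no sign or size of curvature. A gap growing as t²/9 has, on ten annual points, a fitted slope equal to the one entered and loses no power. The footnote also concerns crime alone.
- *80% power holds only if the gap keeps growing to 2018.* The condition is on the fitted average slope. A crime effect of about 9.5% a year that stopped at the end of 2013 would also give 80%, though that lies outside the cited 4–6%.
- *The claim fails for every row.* Crime −6% with growth to the end of 2015 keeps about 78%, and the −2.31% row never claims that 20 areas suffice; it prints 34.
- *The loss arises because the last years carry nearly all the weight.* Leverage for a slope is symmetric about the midpoint of follow-up.
- *Nine years is twice the observed span.* The Background dates the admissions effect to 2015, and no start date is given for the crime data.

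It can also be said that 2013 is the wrong clock, because engagement is studied from 2012. That stands as a limit on the scenarios, which are illustrations and not forecasts. It does not restore the stated power: a gap that starts in April 2012 and grows to 2018 gives about 55% for both crime −5% and admissions −3%. When the effect begins is a separate matter from how long it keeps accruing.

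**Conclusion.** The concern holds as an unsupported planning assumption. Table 4 reaches 80% power at about 20 areas only if the average slope over 2009–2018 matches a yearly rate that the power section reports up to 2013. The protocol does not argue for this, and the Background's 5% total to 2015 conflicts with it. Power for the two effects that 20 areas are meant to detect (crime −5%, admissions −3%) runs from 81% under constant divergence to 62% or 31% if the gap levels off at the end of 2015 or 2013.

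Continued divergence would still not suffice for the prior admissions effect: at −2.31% a year, 20 areas give about 59%.

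These figures assume Table 4's variances are unchanged, quarterly points, and a gap that holds after it stops growing. The protocol does not give the true shape after 2013, so the range is a sensitivity analysis and does not show that the study is underpowered.

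**What to change.** 1. Reconcile the Background and the Power calculations section on the period and size of both source effects: 2013 or 2015 for admissions, 5% in total or 2% a year, and whether the 4–6% for crime is annual.
2. Label the constant slope over 2009–2018 in Table 4 as an assumption, with a reason if there is one.
3. Add rows for a gap that levels off at the end of 2013 and at the end of 2015. These are sensitivity cases; making one of them the base case would swap one unsupported shape for another.
4. Reword the closing sentence to state the resulting range of power at 20 areas per group. Note that the prior admissions effect of −2.31% has about 59% power even under constant divergence.

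The cost is recalculation and wording, and a less favourable stated power. Recruitment does not change.

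### The earlier effects used to justify 20 areas per group are not stated consistently, and even as annual rates 20 per group covers only part of their range

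*Protocol article*

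**What the plan says.** The Background (Alcohol Availability & Harm) summarises two earlier studies of licensing intensity in England. For hospital admissions it reports an "additional 5% reduction in alcohol related hospital admissions rates from 2009 to 2015 (or 2% annually"). For crime it reports "an additional 4–6% reduction in public nuisance and alcohol-related crime rates".

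The Power calculations section cites the same two studies. It gives admissions as 2% a year (95% CI −3% to −2%) up to and including 2013. For crime up to 2013 it says "an additional 4–6% annual decrease was seen in alcohol-related violent crimes, sexual crimes and public order offences".

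Table 4 enters these under the column "Expected average effect size %/year (slope"): 4%, 5% and 6% for crime (29, 19 and 13 areas per group) and 2.31% for admissions (34 per group). A last row gives 3.00% a year as the minimum detectable effect with 20 per group. The section then concludes that 20 plus 20 areas can detect effects in the range that earlier studies found. The next paragraph expects an A&E effect in or around the crime range.

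**The concern.** A 5% reduction over six years and a 2% reduction every year are different quantities, yet one sentence treats them as the same. The power section then gives a different end year for that study. For crime, the unit changes from unstated to annual between the two sections. No text reconciles the figures.

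This matters because the required number of areas varies with one over the slope squared, so a change of unit has a large effect on power. The conclusion about detectable effects also has little room for error: two of the four prior-effect rows in Table 4 already ask for more than 20 areas per group. The Discussion says that null findings could matter as much for policy as positive ones, and that requires established power for plausible effects.

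**Working it through.** **1. Do the stated figures agree?**
- 2% a year over six years (2009–2015): 1 − 0.98^6 = 11.4%, not 5%.
- 5% over six years: 1 − 0.95^(1/6) = 0.85% a year.
- 2% a year reaches 5% after ln 0.95 / ln 0.98 = 2.5 years, a period the article does not mention.
- 4–6% a year over six years: 1 − 0.96^6 = 21.7% to 1 − 0.94^6 = 31.0%.

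**2. Reproducing Table 4.** Inputs from the section: "we assumed a standard level of statistical significance α (5%) and statistical power β (80"%), a two-sided test, follow-up 2009–2018, and the random-slope method ("We used the methodology developed by Edland for power calculations of linear mixed effects models with random slope"). The formula is

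n per group = 2(1.960 + 0.842)² × [slope variance + residual variance / Σ(t − t̄)²] / slope², with (1.960 + 0.842)² = 7.849.

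The number of measurements is not stated, so I used ten yearly points (Σ = 82.5) and 37 quarterly points (Σ = 263.6).
- Crime 4%, yearly: 2 × 7.849 × (0.003 + 0.03/82.5) / 0.04² = 33.0; quarterly 30.5; stated 29.
- Crime 5% (slope 0.05): 21.1 and 19.6; stated 19. The printed slope of −0.04 would give the 4% result, so it looks like a misprint for −0.05.
- Crime 6%: 14.7 and 13.6; stated 13.
- Admissions, slope 0.229: 2 × 7.849 × (0.110 + 0.011/82.5) / 0.229² = 33.0; stated 34.
- Minimum detectable effect, slope 0.296: 19.7; stated 20.

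The quarterly grid comes close to every row. The figures therefore drive the table as annual slopes.

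**3. Power with 20 per group if the annual figures are right.** Power = Φ(slope / √(2V/20) − 1.960), where V is the bracket above.
- Admissions 2.31%: 0.229 / √(2 × 0.1101/20) = 2.182, so Φ(0.222) = 59%.
- Crime 4%: 59% (yearly) to 62% (quarterly).
- Crime 5%: 78% to 81%. Crime 6%: 91% to 93%.
- Effect detectable with 80% power: crime 4.9–5.1% a year; admissions slope 0.294, about 3% a year.

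**4. Power with 20 per group if the figures are totals.** The period is an assumption: four years (2009–2013) to six years (2009–2015). The admissions slope is scaled as 0.229 × annual % / 2.31.

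| | Four years | Six years |
|---|---|---|
| Admissions, 5% in total | 1.27% a year; about 109 per group; power 22% | 0.85% a year; about 243 per group; power 12% |
| Crime, 4% in total | 1.02% a year; about 475–513 per group; power 8% | 0.68% a year; about 1,064–1,149 per group; power 6% |
| Crime, 6% in total | 1.53% a year; about 208–225 per group; power 13–14% | 1.03% a year; about 465–502 per group; power 8% |

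Where a range is shown, it runs between the quarterly and yearly grids.

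**The case against.** A reader might infer that the study was sized on effects several times too large. The article does not support that.

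- It nowhere says that the 4–6% for crime is a total. The Background only leaves out the word annual, and the power section and the Table 4 column both supply it. The earlier work used growth models, which naturally yield annual trends. The crime conflict is therefore an inference from an omission.
- For admissions, the power section gives an interval of −3% to −2% a year, and Table 4's 2.31% lies inside it. Neither 0.85% nor 1.27% does. If one figure is wrong, this points to the 5% summary, which feeds nothing in Table 4.
- The 5% may be another quantity. The Background sentence ends with a counterfactual comparison that carries a further citation. An average gap of 5% over six years would also fit slopes diverging by 5/3 = 1.7% a year.
- Table 4 labels its effect as an average, so its footnote on quadratic trends is not an error in itself.
- The 3.00% row follows from the variances and the number of areas, not from the earlier effects.

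All of this stands. What remains is that the admissions sentence does not add up as written, the units and end years differ between sections, and the conclusion about detectable effects is wider than Table 4 supports even on the annual reading.

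**Conclusion.** The prior effects are stated inconsistently: explicitly for admissions, by inference for crime. The article cannot show which version is right, and its own interval favours the annual admissions figure.

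On the annual reading, Table 4 stands apart from the printed slope of the 5% row. Even so, 20 per group reach about 80% power only from about 3% a year for admissions, the outer limit of the quoted interval, and from about 5% a year for crime. At 2.31% and 4% respectively, power is about 59% and 59–62%.

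On the total reading, with an assumed period of four to six years, power falls to about 12–22% for admissions and 6–14% for crime. The expectation for A&E would fall with crime.

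These figures rest on Table 4's variances and on a yearly or quarterly grid. The 3.00% minimum detectable effect row is unaffected.

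**What to change.** 1. Check the two cited studies. State one effect per outcome, with its unit (per year or total) and period, in the same terms in the Background and in Power calculations.
2. Correct the printed slope of the 5% crime row. If an annual value changes, correct the effect rows of Table 4 on the scale that each row uses. The admissions slope of −0.229 for 2.31% is not a log slope (that would be about −0.023), so it should not be replaced by one without its variances.
3. Add the power with 20 per group for each prior effect.
4. Limit the closing sentence to what 20 per group cover: about 3% a year for admissions and about 5% a year or more for crime. Adjust the A&E paragraph to match.

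The cost is a source check, a re-run of one formula and some wording. The number of areas need not change, though the stated power will look less favourable.
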